**Activation Date**

First approved version: January 13, 2018

**Current Edition:** March 4, 2019

**Trial registration:** The trial was registered with [www.clinicaltrial.gov](http://www.clinicaltrial.gov) (NCT03283124) on Jan 17th, 2018, <https://www.clinicaltrials.gov/ct2/show/NCT03283124>

**Background**

Pelvic organ prolapse (POP) is a common health problem and has significant negative effects on woman's quality of life. The prevalence of symptomatic POP in China is about 9.6% according our national epidemiology study(unpublished). Lower wealth status maybe one of the risk factors for POP [1,2]. Professional society guidelines indicated that transvaginal mesh (TVM) repair should be reserved for high risk patients, such as individuals with recurrent prolapse (particularly of the anterior segment) or with medical co-morbidity that preclude more invasive and lengthier abdominal procedures [3]. The consensus statement in China also proposed that transvaginal polypropylene mesh repair (either commercial pre-cut mesh devices or self-cut mesh) was most appropriate for severe POP (stage III-IV) and recurrent POP [4]. However, the high cost associated with available commercial mesh kits in China (approximately 25,000 RMB) poses a significant challenge for non-directive surgical counselling. Because POP patients in our practice typically have a combination of anterior and apical prolapse, we designed a TVM system in 2006, which included specially designed reusable trocars and self-cut mesh [5]. The mesh pieces used in surgery were cut from a single piece of polypropylene mesh (10 cm×15 cm GyneMesh; Ethicon, Somerville, NJ, USA). A Seven-year prospective cohort study indicated that self-cut TVM repair had a good long-term results, with 84.3% anatomic success (POP-Q stage 0 or I) and 8.9% mesh-related complication [6]. This result was in line with mesh-kit surgical repair for POP reported by other surgeons. From 2006 to 2008, The gynecology department of Peking Union Hospital in Beijing, China conducted a multicenter prospective trial to evaluate the anatomic and quality-of -life outcomes in treatment of severe POP with self-cut TVM repair [7]. In this prospective case-series, the anatomical success was 91.7%, and there were clinically and statistically significant improvements in quality-of-life. Mesh exposure or erosion rate was 6.9%. It appeared that our TVM procedure with self-cut mesh was safe and effective in treatment of severe POP with less cost when compared with mesh-kit procedures.

Titanium-coated meshes are new products in POP repair, which improved the pelvic floor-related quality of life and sexual function in a prospective multicenter trial

[8]. Fünfgeld et al reported a large prospective multicenter study in Germany, with 289 patients who underwent surgery with a titanium-coated polypropylene mesh-kit (TiLOOP® Total 6, pfm medical ag) and were followed up for a median of 36 months [9]. The recurrence rate for the anterior compartment was 4.5 %, and the quality of life improved significantly. The erosion rate was 10.5% (30/286). From Aug 2015, we began to use Titanium-coated mesh and we reported the results of 18 patients who followed up at mean 10.9 months (4-17months) with an objective success rate of 100% , and no exposure of mesh or erosion after surgery[10].

We did not find studies comparing self-cut titanium coated mesh procedures with mesh-kit procedures in patients with POP. The aims of the research are to demonstrate whether self-cut mesh procedure is non-inferior to the mesh-kit procedure and to investigate the performance of titanium coated mesh for vaginal prolapse repair.

## **Methods/ Design:**

### **Study objective**

The aim of this RCT is to compare the outcomes of self-cut versus mesh kit titanium-coated polypropylene transvaginal mesh repair in the treatment of POP. Our primary outcome is composite success rate at 1 year, with secondary outcomes including perioperative parameters, disease-specific quality of life and sexual function instruments, complications and cost.

### **Hypothesis**

1. The composite outcome of TVM repair using self-cut mesh will be non-inferior to the TVM repair using mesh-kit.
2. TVM repair using self-cut mesh will be non-inferior to the TVM repair using mesh-kit with respect to disease-specific quality of life, sexual function scores and complications.
3. The TVM repair using self-cut mesh will be associated with lower total hospital charges than the TVM repair using mesh-kit.

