### **Statistical analysis**

#### **sample size and power considerations**

The aim of the trial is to test the hypothesis that procedure with self-cut mesh is non-inferior to the procedure with a mesh kit in terms of the composite success rate and safety. According to Fungfeld's report, the anatomic success rate (POP-Q stage  $\geq$  II, different from this proposed study) after 12 months across all compartments was 86% [8]. Based on a success rate of 90% in this study and 10% as the non-inferiority margin (beta 0.2 and one-sided alpha 0.025), 284 patients (142 in each group) would be required. Taking into account 10% who do not continue to the 1-year follow-up visit, a total of 312 patients will be recruited. the procedure with self-cut mesh will be considered non-inferior if the lower limit of the 95% confidence interval in success rates lies above the non-inferiority margin of -10%.

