### **Data analysis**

Data was analyzed on an intention-to-treat basis. Frequency and percentages were used to describe categorical variables, Fisher's exact test used to compare treatment groups, and logistic regression used to estimate odds ratios (ORs), and associated 95% confidence intervals (95% CIs). Means and standard deviations (SDs) were used to describe approximately normally distributed continuous data. Analysis of covariance (ANCOVA) was used to compare treatment groups at 1 years after

procedure adjusting for baseline values and to estimate mean differences between treatment groups and associated (95% CI). Medians and range (minimum, maximum values) were used to describe non-normally distributed continuous data, Wilcoxon rank sum test used to compare treatment groups and Student t test to estimate mean differences and associated (95% CI). Paired t tests were used for differences between pre- and post-measurements. For the primary outcome, we will also perform subgroup analysis based on body mass index (BMI) ( $< 24$ ,  $\geq 24$ ), history of POP procedure(primary, recurrent), or prolapse stage (stage 3, stage 4). Analyses will be performed for each subgroup in a similar way to the primary analysis. AEs will be listed and analyzed using a  $\chi$ -squared test or Fisher's exact test. Severe AEs will be listed and described in detail.

All data will be analyzed with SPSS 21.0 (IBM, Chicago, IL, USA) software packages. Statistical significance is defined as a two-sided P value of  $< 0.05$ .

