### **Justification of the sample size**

The aim of the trial is to test the hypothesis that the procedure with self-cut mesh is non-inferior to the procedure with a mesh kit in terms of the composite success rate and safety. According to Fünfgeld et al.'s report, the anatomic success rate (POP-Q stage  $\geq$  II, different from this proposed study) after 12 months across all compartments was 86%. Based on a success rate of 90% in this study and 10% as the non-inferiority margin ( $\beta = 0.2$  and one-sided  $\alpha = 0.025$ ), 284 patients (142 in each group) would be required. Taking into account 10% who do not continue to the 1-year follow-up visit, a total of 316 patients will be recruited. The procedure with self-cut mesh will be considered non-inferior if the lower limit of the 95% confidence interval in success rates lies above the non-inferiority margin of -10%. The enrollment will be more than 10 patients in each center.

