### **Description of analyses**

#### Primary outcome

The primary outcome measure is a composite surgical success variable measured at 1 year after surgery, defined as follows:

1. Absence of vaginal bulge symptoms as indicated by a rating of 0 on question 3 of the Pelvic Floor Distress Inventory-20 (PFDI-20): "Do you usually have a bulge or something falling out that you can see or feel in your vaginal area?"
2. No additional re-treatment (surgical or not) for POP
3. No POP-Q point at or beyond the hymen (i.e., Aa, Ba, C, Ap, Bp all < 0 cm)

All estimated difference with their 95% confidence intervals in primary outcome will be reported, the Agresti-Coull method will be used to calculate 95% CIs for differences in proportions.

We will apply multiple imputation techniques (five imputed datasets) for all women with missing data on primary outcome. Robustness of primary outcome will be

evaluated in sensitivity analyses performed in the ITT population without imputation. We will also conduct a secondary analysis of primary outcome based on per-protocol population, which excludes all patients who had a protocol deviation.

The secondary outcomes

- Anatomic outcome (POP-Q score) of each vaginal segment
- Symptomatic improvement-relief of symptoms of pelvic floor disorders, including urinary, bowel and sexual function using validated instruments
- Intraoperative parameters
- Complications
- Costs, defined as the direct total charges for the surgical admission including operation, medication and use of materials (e.g., surgical mesh)

We will consider the independent sample test or the non-parametric Mann-Whitney test for continuous outcomes, and the  $\chi^2$  test or Fisher's exact test for categorical outcomes. We will use paired sample t test to compare mean continuous data within groups. For anatomic outcomes (POP-Q score) and symptomatic improvement outcomes, we will compare the changes from baseline to 1-year follow up.

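### Hypothesis 2 and the safety aim claim non-inferiority without a margin or decision rule, so the planned analyses cannot establish them

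*Combined protocol and SAP*

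**What the plan says.** **The claims.** Under Hypothesis, item 2, the protocol says self-cut repair "will be non-inferior to the TVM repair using mesh-kit with respect to disease-specific quality of life, sexual function scores and complications". The sample-size text, in the protocol and in both SAPs, describes the aim as showing the self-cut procedure to be "non-inferior to the procedure with a mesh kit in terms of the composite success rate and safety".

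**The margin and rule.** The sample size is "Based on a success rate of 90% in this study and 10% as the non-inferiority margin", with 80% power, one-sided alpha 0.025 and 142 women per group. Non-inferiority is declared when the "lower limit of the 95% confidence interval in success rates lies above the non-inferiority margin of -10" percentage points. Both statements concern the success rate. No section gives a margin, power or decision rule for quality of life, sexual function or complications.

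**The analyses.** For secondary outcomes the final SAP (Description of analyses) says: "We will consider the independent sample test or the non-parametric Mann-Whitney test for continuous outcomes". It adds chi-squared or Fisher tests for categorical outcomes and paired t tests within groups. Its statement on confidence intervals of the difference covers the primary outcome only. Its Analysis principles add covariate-adjusted regression if the arms are imbalanced at baseline.

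In the protocol's Data analysis section, "AEs will be listed and analyzed using a" chi-squared or Fisher's exact test, with significance at two-sided P<0.05. The same section also plans odds ratios from logistic regression and ANCOVA mean differences, each with a 95% confidence interval.

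**The concern.** A non-inferiority hypothesis needs a stated largest acceptable disadvantage and a rule that excludes it, usually through a confidence limit. The plan supplies both for Hypothesis 1 and neither for Hypothesis 2 or for safety. A test of no difference cannot fill the gap: it puts the burden of proof on showing harm, and the less information there is, the more readily it returns a non-significant result. The within-group paired tests do not compare the arms at all.

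The stake is the safety half of the trial's message. The protocol's Discussion says that non-inferiority could justify recommending self-cut mesh because it costs patients less, and the stated aim makes safety part of that non-inferiority. The Background reports mesh exposure or erosion of 6.9% and 10.5% in earlier series, so mesh harm is not a marginal outcome.

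**Working it through.** **1. The plan's own figure.** Inputs from the sample-size sections: success 90% in both arms, margin 0.10, one-sided alpha 0.025, power 0.80.

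n per arm = (1.96 + 0.8416)² × 2 × 0.90 × 0.10 / 0.10² = 7.849 × 0.18 / 0.01 = 141.3, so 142 per arm and 284 in all. Then 284 / 0.90 = 315.6, or 316, as in the SAP. The figure reproduces, and it covers the primary outcome only.

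**2. Base rates for complications, from the Background.** 6.9% (mesh exposure or erosion, multicentre self-cut series), 8.9% (mesh-related complications, seven-year self-cut cohort), 10.5% (erosion, 30/286, titanium-coated kit series). These differ in follow-up and definition, so they serve as a range.

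**3. How often a difference test misses a true excess.** With 142 per arm and true rates p0 (kit) and p1 (self-cut):

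P(miss) = Σ over i, j of Bin(i; 142, p0) × Bin(j; 142, p1) × [two-sided P ≥ 0.05 for i/142 v j/142]

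| Kit rate | Doubled rate | Fisher misses | Chi-squared misses (uncorrected) |
|---|---|---|---|
| 6.9% | 13.8% | 59% | 52% |
| 8.9% | 17.8% | 46% | 39% |
| 10.5% | 21.0% | 37% | 31% |

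For a true excess of 5 points, Fisher misses 76%, 79% and 81% at the three rates; chi-squared misses 70% to 76%. With the SAP's full 316 and no dropout (158 per arm), Fisher's power for the doubling from 6.9% is 0.456, so it still misses 54%.

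**4. An illustrative result.** Take 20/142 self-cut v 10/142 kit. The difference is 0.1408 − 0.0704 = 0.0704. SE = √(0.1408 × 0.8592/142 + 0.0704 × 0.9296/142) = 0.0362. The 95% CI is 0.0704 ± 1.96 × 0.0362, or −0.1 to +14.1 points. Fisher gives P = 0.081 and uncorrected chi-squared P = 0.054. Neither is significant, yet a 14-point excess is not excluded.

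**5. Margins that 142 per arm could support.** With equal true rates p, 80% power and one-sided 0.025, margin = 2.8016 × √(2p(1 − p)/142):

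- 6.9%: 2.8016 × 0.0301 = 8.4 points
- 8.9%: 2.8016 × 0.0338 = 9.5 points
- 10.5%: 2.8016 × 0.0364 = 10.2 points

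For an assumed margin of 5 points, n per arm = 7.849 × 2p(1 − p)/0.05² = 404, 510 and 591.

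**6. Questionnaire scores, in SD units.** Margin = 2.8016 × √(2/n), which is 0.33 SD at n = 142. PISQ-12 is given only to sexually active women, and their number is not stated. An assumed 70 or 30 per arm would support 0.47 or 0.72 SD. A true deficit of 0.3 SD would be non-significant about 29% of the time at 142 per arm, and 57% or 79% at 70 or 30.

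**The case against.** Three stronger readings are tempting, and the documents do not support them.

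- A reader might infer that the trial will take P>0.05 as proof of non-inferiority. No section says so; the protocol only defines statistical significance. What the documents show is that no other criterion is supplied.
- A reader might infer that difference tests are the only analyses planned. That is roughly true of the SAP's unadjusted secondary analyses, but not of the protocol, whose odds ratios and ANCOVA mean differences come with 95% intervals. Those intervals could carry a non-inferiority assessment if margins were set.
- A reader might infer that a doubling of complications would most likely go undetected. With either test that holds only at 6.9%. At 8.9% and 10.5%, the latter being the rate reported for the kit used as control, detection is more likely than not.

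It can also be said that these outcomes are secondary, that the primary test is unaffected, and that safety has other scrutiny: detailed description of severe events, monitoring board review of mesh-related events, and standard complication coding. All of this stands, and it lowers the severity. None of it supplies a margin or a rule, so the core point remains.

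**Conclusion.** The concern holds in a limited form. The protocol states a non-inferiority hypothesis for quality of life, sexual function and complications, and a non-inferiority aim for safety, that its planned analyses cannot establish. A non-significant difference test would be weak evidence: Fisher misses 37% to 59% of true doublings and about four in five true 5-point excesses (chi-squared 31% to 52%, and 70% to 76%).

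These figures assume 142 analysed women per arm and base rates taken from earlier series. The 5-point excess, the SD-unit deficits and the numbers of sexually active women are illustrative assumptions. The conclusion that margin and rule are missing depends on none of them. This should be fixed, but it does not threaten the primary analysis.

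**What to change.** - **Protocol.** Restate Hypothesis 2 as a descriptive between-arm comparison, and remove safety from the powered non-inferiority aim there and in the SAP's sample-size section.
- **SAP.** Report complications, overall and mesh exposure separately, as risk differences with 95% confidence intervals. Report PFDI-20, PFIQ-7 and PISQ-12 as baseline-adjusted mean differences with 95% confidence intervals, carrying over the ANCOVA already in the protocol.
- **Interpretation.** State that P>0.05 on these outcomes will not be described as non-inferior.
- **If a non-inferiority claim is kept for any of them.** Fix a justified margin and a confidence-limit rule before any between-arm outcome data are examined. Patients and surgeons know the allocation, so the safeguard is that date rather than unblinding. The margins in step 5 show what the present size can bear; for complications it is about 8 to 10 points.

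The cost is wording and a few extra table columns, with no new patients, visits or data. The downside is a more modest secondary claim.

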### **Study design**

The trial is a randomized controlled multi-center non-inferiority trial. The study protocol and informed consent was approved by the institutional review board of Peking Union Medical College Hospital. The trial was registered with [www.clinicaltrial.gov](http://www.clinicaltrial.gov) (NCT03283124). Patients will be recruited from 11 hospitals at Tier III level in China. The gynecology department in each participating hospital performed at least 50 POP surgeries each year. In order to facilitate research development beyond this single trial, a new electronic data capture (EDC) system was co-developed with a CRO [LinkDoc Beijing company] and they will be responsible for data management. The CRO will have no role in the analysis of the data or the eventual production of any research manuscripts.

All women eligible at each center will be invited to participate. It is not possible to blind surgeons to the allocated surgical procedure. Women were not able to be blinded because payment for the cost of the implant is paid directly to the hospital by the patient, and they necessarily informed about the difference in cost between the two mesh products as part of the consent process. An independent staff or a research nurse who was not involved in treatment will carry out the questionnaires collection and follow-up POP-Q measurement. A figure showing the planned visit and examination schedule is presented in Fig.1 and Fig.2.

### **Participating hospitals**

The trial will be performed in 11 hospitals in China: Peking Union Medical College Hospital; Wuxi Maternal and Child Health Care Hospital; Changsha Maternal and Child Health Care Hospital; Foshan Maternal and Child Health Care Hospital; The First Affiliated Hospital of Guangzhou Medical College; The second Xiangya Hospital of Central South University; Qilu Hospital of Shandong University; Shanxi Provincial People's Hospital; Sichuan University West China Second University Hospital; the First Affiliated Hospital of Xinjiang Medical University; the People's Hospital of Xinjiang Uygur Autonomous Region.

In order to minimize performance bias, only surgeons with an adequate experience in TVM procedures (more than 20 cases per year) will serve as primary surgeon in this

trial. Since the only difference between the two arms involves modest differences in the equipment used, all surgeons will be able to perform both procedures. POP diagnosis, POP-Q measurement, questionnaires and standardized procedures will be trained in a standardized fashion. To ensure standardization for all participating centers, a video containing the crucial steps of the consent process will be used.

### **Study population and recruitment**

Inclusion criteria:

1.Symptomatic POP with apical and/or anterior vaginal prolapse stage III-IV. Only patients with moderate posterior vaginal prolapsed stage I-II ( $C > +1\text{cm}$  or  $Ba > +1\text{cm}$ , with  $Bp \leq +1\text{cm}$  by the POP-Q) will be included. Those with Stage III-IV posterior prolapse will be excluded.

2.Subjects must be more than 3 years after menopause or more than 55 years old, and less than 75 years old.

3.Subject chooses transvaginal mesh treatment after appropriate surgical counselling.

4. Subject is willing and able to comply with the follow-up regimen.

5.Subject is capable of providing informed consent.

Exclusion criteria:

1. High surgical risk due to medical co-morbidities such as, active gynecologic and urinary tract infection, anticoagulation treatment or coagulation disorders, prior pelvic radiation therapy, neurologic or medical condition affecting bladder and bowel function (e.g., multiple sclerosis, spinal cord injury or stroke with residual neurologic deficit), chronic pelvic pain.

2. Need for concomitant anti-incontinence procedure. We want to minimize the interference of other procedures.

Women eligible for this trial will be provided with the information on the objectives, designs, methods, possible advantages and disadvantages of the treatment, and they can refuse or withdraw at any time with no consequences for their treatment. Before randomization, written informed consent will be obtained.

## **Primary and secondary outcomes**

The primary outcome measure will be a dichotomous, composite surgical success variable measured at 1 year after surgery. The composite success definition of surgical outcome includes:

1. Absence of vaginal bulge symptoms as indicated by a rating of 0 on question 3 of the pelvic floor distress inventory-20 (PFDI-20): "Do you usually have a bulge or something falling out that you can see or feel in your vaginal area?" AND

2. No additional re-treatment (surgical or not) for POP. AND

3. No POP-Q point at or beyond the hymen (i.e. Aa, Ba, C, Ap, Bp all < 0 cm).

The secondary outcomes will include:

1. Evaluation of anatomic outcome (POP-Q score) of each vaginal segment.

2. Symptomatic improvement: relief of symptoms of pelvic floor disorders, including urinary, bowel and sexual function using validated instruments collected postoperatively.

3. Intraoperative parameters.

4. Complications.

5. Cost. The direct total charges for the surgical admission including operation, medication and use of materials (e.g. surgical mesh).

## **Randomization**

After informed consent is signed, the patients will be registered on the web-based EDC system by a research staff to allocate each a unique study number prior to randomization. Research staff will access the system and, using the study number and initials, request randomization. Patients are randomized in a 1:1 ratio to either "self-cut mesh" group or "mesh-kit" group, according to a computer-generated randomization sequence with a block size of six. Randomization will be stratified according to centers. The patient and surgeon will be informed about the allocated operative procedure after the randomization.

